#### **GDF-15**

Based on data by Wollert et al (17), and estimating the standard deviation using Wan et al (15) to be 780, we will be able to detect a mean difference in GDF-15 of 240ng/L between

[figure not shown]University Hospitals of Leicester  
NHS Trust

## RapidNSTEMI Biomarkers v1.0

the groups. For GDF-15, the 99th percentile cut-off point determined previously in a healthy reference population is 1200ng/L (17). Published data has demonstrated median GDF-15 levels in N-STEMI to be 1499ng/L (17).

### ST-2

Based on data by Eggers et al (14), and estimating the standard deviation using Wan et al (15) to be 20, we will be able to detect a mean difference in ST-2 of 6U/ml between the groups. For ST-2, the 99th percentile cut-off point determined previously in a healthy reference population is 31U/ml in men and 21U/ml in women (18). Median levels in patients diagnosed with N-STEMI are 28U/ml with 45% of patients noted to have elevated levels at the point of diagnosis when taking into account gender-specific upper reference levels (14). Again, there are no available data in patients with non-obstructive coronary disease.

The above statistical calculations aim to provide power for the selected biomarkers to predict a clinically meaningful difference between the two groups in whom we are interested; those with obstructive coronary artery disease that require PCI following diagnostic angiography, and those that do not. This is a novel study, and consequently there is limited literature supporting the differences we are likely to see between these two groups. Any results are likely to be hypothesis generating. Despite this, we feel these differences are of clinical importance and hence our proposed sample size of 550 patients is sufficient for our aims.

### Statistical analysis

Summary statistics including counts and percentages will be provided for all categorical variables and means and standard deviations for normally distributed continuous variables and medians and interquartile ranges for non-normally distributed continuous variables. The differences in the levels of the biomarkers between the two groups (PCI vs no PCI) will be initially analysed using a two-sample t-test. Appropriate transformations will be made to non-normally distributed variables. Subsequently, multiple linear regression will be performed to adjust for potential confounders (including age and sex). Adjusted means, mean differences, 95% confidence intervals (CIs) and p-values will be provided for comparisons across the two groups.

Based on the previous results showing significant differences between the groups for these novel biomarkers, Receiver Operating Characteristic (ROC) analyses will be performed in order to determine the optimal cut-off points for each biomarker for the requirement of PCI. That is, the cut-point which best provides the best balance between sensitivity (proportion of true positives) and specificity (proportion of true negatives) for the level of biomarker as a diagnostic tool. Sensitivities, specificities and area under the curves will be reported for these cut-offs.

In addition to the above analyses, correlations and comparisons will also be reported between these novel biomarkers and troponin. Clinical outcomes comparing those who do and do not require PCI will be analysed univariately and multivariately with logistic regression. All data will be analysed using the R environment for statistical computing (19).

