### **3. Aims of substudy**

The RapidNSTEMI Biomarkers substudy aims to explore the association between hs-Tn, the tested novel biomarkers, and clinical outcomes in higher-risk NSTEMI patients recruited to the main RapidNSTEMI trial.

Primary aim:

- To investigate in patients with a clinical diagnosis of NSTEMI, the sensitivity and specificity of novel biomarkers (cMyC, GDF-15 and ST-2) in predicting which patients do or do not require PCI following diagnostic angiography.

Secondary aims:

- Correlate levels of each biomarker with cTn taken in the same patient
- Comparative predictive value of each biomarker for primary and secondary main trial outcome measures, and to include in-hospital, 30-day and 6-month rates of major adverse cardiovascular events
- Comparison between biomarkers for predictive values
- Impact of PCI on each biomarker release and subsequent future clinical outcomes
- Positive and negative prediction for type of myocardial infarction (Type 1, Type 2, Type 4a)
- Development of a multivariate model combining candidate biomarkers with risk stratification scoring criteria (e.g. GRACE score) to produce an optimal predictor of clinical outcome

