### **4. Statistics and power calculations**

#### **Sample size**

With the available resources we will be able to collect and analyse two samples (pre and post-angiography) from 550 patients. It is expected that approximately two-thirds of patients in our cohort will require PCI. If we recruit 550 patients, we expect approximately 367 to require PCI and 183 to not. Based on these 550 patients, 80% power and a 5% significance level, we can calculate the following for the three novel biomarkers.

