#### **cMyC**

Based on data by Kaier et al (9), and estimating the standard deviation using Wan et al (15) to be 430, we will be able to detect a mean difference in cMyC of 132ng/L between the groups. For cMyC, the 99th percentile cut-off point determined previously in stable patients without obstructive coronary artery disease referred for invasive angiography is 87ng/L (16). Patients diagnosed with acute myocardial infarction were found to have median levels of 237ng/L (9).

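### Appendix VI makes the ROC analysis depend on significant t-tests, although the sensitivity and specificity of all three biomarkers are the sub-study's primary aim

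*Protocol*

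**What the plan says.** Section 3 of Appendix VI gives one primary aim, covering three markers without ranking them: to investigate "the sensitivity and specificity of novel biomarkers (cMyC, GDF-15 and ST-2) in predicting which patients do or do not require PCI following diagnostic angiography". Protocol section 7.2.2 lists the same quantity among the trial's secondary outcomes. Neither place makes it conditional on another result.

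Section 4 of Appendix VI sets out the analysis. Marker levels in patients who do and do not have PCI are compared by a two-sample t-test, then by linear regression adjusted for confounders, with p-values. The text continues: "Based on the previous results showing significant differences between the groups for these novel biomarkers, Receiver Operating Characteristic (ROC) analyses will be performed". The rest of that sentence says the purpose is to find the best cut-off for each marker. Sensitivities, specificities and areas under the curve are then reported at those cut-offs. Nothing covers a marker whose groups do not differ significantly.

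On sample size the section says "If we recruit 550 patients, we expect approximately 367 to require PCI and 183 to not", and then "Based on these 550 patients, 80% power and a 5% significance level, we can calculate the following for the three novel biomarkers". On status, the ST-2 paragraph says "Any results are likely to be hypothesis generating".

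Section 7 of Appendix VI lists two samples per patient, one at admission and one after angiography with or without PCI. The statistical analysis text does not say which is used to compare the PCI and no-PCI groups.

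**The concern.** The t-test asks whether mean levels differ. The primary aim asks how well a marker separates patients who need PCI from those who do not. Making the second depend on the first lets a test result decide whether a pre-specified outcome is reported. A marker that fails leaves a gap in the primary aim. A marker that passes is seen only when its observed separation is large enough to be significant, which biases the reported AUC upward.

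This matters because the clinical implications paragraph of Appendix VI looks ahead to a marker panel that would spare some patients angiography. For that use, a clear negative result on a marker is as informative as a positive one.

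The unnamed sampling time raises a related problem. A sample drawn after PCI cannot predict the need for it. Section 3 also lists the effect of PCI on marker release as a separate secondary aim, so the two uses of the samples need to be kept apart.

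**Working it through.** **1. The texts side by side.** Section 3 of Appendix VI and protocol section 7.2.2 promise sensitivity and specificity for the novel markers, without condition. Section 4 bases the analysis that produces them on significant group differences. The later mention of each marker does not remove the condition: the sentence either assumes all three will be significant or limits the ROC step to those that are. Both readings leave a non-significant marker uncovered.

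**2. Inputs.** From section 4 of Appendix VI: 367 v 183 patients, 5% level, 80% power, and SDs of 430 (cMyC), 780 (GDF-15) and 20 (ST-2). The section does not say whether the test is one- or two-sided; two-sided is assumed here.

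**3. What a significance condition would do.** The standard error of a mean difference in SD units is √(1/367 + 1/183) = 0.0905. To pass, the observed difference must exceed 1.96 × 0.0905 = 0.177 SD. If marker levels are normal with equal variance, that corresponds to an AUC of Φ(0.177/√2) = Φ(0.125) = 0.55.
- A marker with no true difference fails 95% of the time and would have no ROC result.
- In the remaining 5% its observed AUC is 0.55 or more, or 0.45 or less, against a true 0.50.

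**4. The printed detectable differences.** For cMyC the section estimates the SD "to be 430, we will be able to detect a mean difference in cMyC of 132ng/L between the groups". For GDF-15 it prints 240 ng/L, and for ST-2 6 U/ml. The formula is (1.960 + 0.842) × SD × 0.0905, which with unrounded values is 2.8016 × SD × 0.09049.

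| Marker | SD | Printed | From stated inputs | Power at printed value, 5% |
|---|---|---|---|---|
| cMyC | 430 | 132 | 109.0 | 92.4% |
| GDF-15 | 780 | 240 | 197.8 | 92.5% |
| ST-2 | 20 | 6 | 5.07 | 91.2% |

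The printed values are not reproduced. With 80% power and the stated group sizes they imply two-sided levels of about 1.1%, 1.1% and 1.3%.

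**5. Three unadjusted tests.** If all three markers were null, the chance of at least one p < 0.05 is 1 − 0.95³ = 14.3% under independence. The protocol gives no correlation between the markers. Assuming equal correlation between the three test statistics:

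| Correlation | 0 | 0.3 | 0.5 | 0.7 | 0.9 |
|---|---|---|---|---|---|
| At least one p < 0.05 | 14.3% | 13.6% | 12.5% | 10.9% | 8.4% |

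If only two markers are null and independent, it is 1 − 0.95² = 9.75%.

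**6. Room for a three-way split.** At 0.05/3 = 1.67% per marker, the multiplier becomes 2.394 + 0.842 = 3.236. The detectable differences are then 125.9, 228.4 and 5.86, and power at the printed differences is 84.1%, 84.3% and 82.2%. The split fits inside the printed values only because those values exceed what the stated inputs give. If 10% of samples were lost (an assumption), the detectable differences under the split would be 132.7, 240.7 and 6.17, just above the printed values.

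**The case against.** The best defence is that the sentence is loosely written and not a rule. It goes on to speak of a cut-off for each marker, no marker-by-marker pass or fail is set out, and the aim and outcome lists are unconditional. An investigator could reasonably run the ROC analysis on all three. AUC is also to be reported, so a useless marker carried forward would tend to show a value near 0.5. Much of this stands: selective reporting follows from the wording but is not declared as an intention. It does not remove the point, because the sentence still presupposes significance and is silent on the other case.

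A reader might infer something stronger: that the sub-study runs three co-primary tests with an inflated error rate and must control it. The documents do not support that. They claim no family-wise 5%, they have no rule that the sub-study succeeds if any one marker is significant, and they call the results likely to be hypothesis generating. Any single inflated figure needs a correlation that is not given and assumes that all three markers are null. Multiplicity handling may also sit in an analysis plan that is not at hand.

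A reader might also count six tests, on the ground that two samples are taken. Nothing says the PCI v no-PCI comparison is to be made at both times. The stated purpose of avoiding angiography, and the separate aim on marker release after PCI, point to the admission sample for prediction.

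**Conclusion.** The point holds as a wording fault with a real consequence: section 4 of Appendix VI conditions a pre-specified outcome on a t-test result. If the condition is applied marker by marker, a null marker goes unreported 95% of the time and otherwise appears with an observed AUC at least about 0.05 from 0.5. That size rests on two-sided tests, normal marker levels with equal variance, and the planned 367 v 183. Transforming the data, which the section allows, would carry the argument to the transformed scale.

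Multiplicity is a side note. The chance of at least one nominally significant result is about 8% to 14% if all three markers are null, over assumed correlations from 0 to 0.9. For an exploratory sub-study, clear labelling is enough.

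The mismatch between the printed 132, 240 and 6 and the recomputed 109, 198 and 5.1 is a separate error in the same section, and its cause cannot be told from the document. None of this touches the trial's primary outcome.

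**What to change.** In section 4 of Appendix VI:

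1. Delete the significance condition. State that AUC, sensitivity and specificity, with 95% confidence intervals, will be reported for cMyC, GDF-15 and ST-2 whatever the t-tests show.
2. Name the admission (pre-angiography) sample as the one used to compare the PCI and no-PCI groups and for the ROC analysis. Keep the post-angiography sample for the secondary aim on marker release.
3. Label the three p-values unadjusted and exploratory. Holm's procedure across the markers is an option, not a requirement.
4. Restate the detectable differences so that they follow from the stated level, power and group sizes (about 109 ng/L, 198 ng/L and 5.1 U/ml), or state the inputs that give 132, 240 and 6.

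The cost is wording in the appendix and its analysis plan, with no extra patients, samples or assays. Only the optional Holm step would affect power. Under plain Bonferroni, power at the printed differences falls from 91–92% to 82–84%, with little margin for lost samples.

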### 7.1 AIMS OF THE STUDY

This study will aim to answer the following questions:

- In N-STEMI ACS patients who are shown to be at higher-risk (GRACE score  $\geq 118$  or  $\geq 90$  with additional high risk features), does immediate angiography with a view to follow on revascularisation significantly improve outcomes (efficacy and safety) compared to angiography with follow on revascularisation at routinely used timing?
- Will any benefits correlate with degree of estimated risk (i.e. will the highest GRACE 2.0 score patient benefit most)?
- Is an early intervention strategy cost effective?
- Can mechanistic understanding be gained from CMR sub-study?
- Can novel biomarkers predict need for PCI and future clinical outcomes?
- Will longer term “passive” follow up through NHS Digital show an improvement in outcomes?

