### 7.13 BIOMARKERS SUBSTUDY (APPENDIX VI)

A substudy testing selected novel biomarkers will be performed in accordance with the Biomarkers substudy protocol attached in Appendix VI. It is anticipated that the Biomarkers substudy will be performed in selected sites. Key outcome measures for the substudy include the predictive ability of the selected biomarkers for obstructive coronary artery disease and requirement of PCI, and main trial clinical outcome measures.

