## RapidNSTEMI Biomarkers v1.0

[figure not shown]

7. Well validated threshold differentiating between normal (healthy) and abnormal (disease state positive)

The RapidNSTEMI main study is a prospective randomised controlled trial designed to test the hypothesis that very early angiography with, where appropriate, revascularisation in higher-risk NSTEMI patients will improve clinical outcomes compared with standard care.

The Biomarkers substudy is designed to assess the levels of novel biomarkers in this higher risk NSTEMI population, thereby allowing direct comparison with measured contemporary hs-Tn. Subsequent correlation of these biomarkers with clinical outcomes, and investigation into their potential as predictors of coronary artery disease requiring PCI, will also be assessed to determine whether they are candidates to improve future clinical stratification and triage. Additionally, the unique aspect of participant randomisation to differing treatment strategies will allow direct evaluation of novel biomarker release according to timing of PCI and the impact of procedural related injury on outcomes. Such analyses may allow the identification of these new biomarkers as plausible candidates to refine care pathways in the future.

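### The biomarker sub-study's one stated regression with a clinical outcome as response compares PCI with no PCI and names no biomarker, so it does not test the secondary aim that biomarkers predict outcome

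*Protocol*

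**What the plan says.** The aim that biomarkers predict outcome appears in several places in the protocol.

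- Section 7.1 asks "Can novel biomarkers predict need for PCI and future clinical outcomes".
- Section 7.13 gives the key sub-study measures as predictive ability for obstructive disease, "requirement of PCI, and main trial clinical outcome measures".
- Appendix VI, section 1, promises "Subsequent correlation of these biomarkers with clinical outcomes".
- Appendix VI, section 3, lists among its secondary aims "Comparative predictive value of each biomarker for primary and secondary main trial outcome measures" and "Development of a multivariate model combining candidate biomarkers with risk stratification scoring criteria (e.g. GRACE score) to produce an optimal predictor of clinical outcome".

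The primary aim in section 3 is different. It concerns sensitivity and specificity "in predicting which patients do or do not require PCI following diagnostic angiography".

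Appendix VI, section 4 (Statistical analysis), then states the methods. It starts with biomarker levels: "The differences in the levels of the biomarkers between the two groups (PCI vs no PCI) will be initially analysed using a two-sample t-test", followed by linear regression. ROC analysis with requirement for PCI as the endpoint comes next, then correlations and comparisons of the biomarkers with troponin. Clinical outcomes enter in one sentence only: "Clinical outcomes comparing those who do and do not require PCI will be analysed univariately and multivariately with logistic regression".

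**The concern.** A model that compares outcomes between patients with and without PCI has as its null that the two groups have equal odds of an event. The prognostic aim needs another null: that the odds of an event do not depend on biomarker level. A result for the first says nothing about the second.

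The same section 3 also has a secondary aim on how PCI affects biomarker release and later outcomes, and the sentence may have been written for that. It does not serve that aim either. Section 7.8 leaves the choice of PCI, CABG, medication or no further treatment to the interventionist at angiography. The contrast therefore compares kinds of patient, not the effect of a procedure.

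At stake is the prognostic half of one of the six questions in section 7.1. An analyst who follows section 4 as written produces no biomarker-outcome estimate. An analyst who adds one must choose the lead outcome, the sample and the adjustment with no protocol text to point to, possibly after the stored samples have been assayed.

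**Working it through.** **1. Aims against analyses.** The main check is a reading of section 3 against section 4 of Appendix VI.

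| Aim (section 3) | Matching analysis (section 4) |
|---|---|
| Primary: biomarkers predict need for PCI | t-test, linear regression, ROC: matched |
| Biomarkers against troponin | Correlations and comparisons: matched |
| Biomarkers predict main-trial outcomes and MACE | None; the outcome regression has PCI as its contrast |
| Combined biomarker-plus-GRACE outcome model | None |
| Effect of PCI on biomarker release and later outcomes | Outcome regression on PCI status, confounded by indication |

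No analysis in section 4 has a biomarker on one side and a clinical outcome on the other.

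**2. Who is in the no-PCI group.** Section 4 expects 550 patients, 367 needing PCI and 183 not. Section 6.5 and Appendix VII describe patients with normal coronary arteries, patients treated medically, and about 8% sent for CABG. The appendix does not say where CABG patients belong. If they count as no PCI, that is 0.08 × 550 = 44 of 183, or 24% of the group. Unobstructed and surgical disease would then sit together, which is a further reason not to read the contrast as an effect of PCI.

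**3. The plan's own figures.** The power statements in section 4 concern biomarker levels by PCI status; none concerns outcomes. For cMyC (SD 430, 80% power, 5% level, taken as two-sided) the normal approximation gives (1.96 + 0.842) × 430 × √(1/367 + 1/183) = 109 ng/L, against 132 stated. The stated figure is thus conservative, and this separate discrepancy has no bearing here.

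**4. What a biomarker-outcome model could detect.** Assume the sub-study has the main trial's planning rates in section 8.1. The average is (19% + 14.25%)/2 = 16.625%, so 550 × 0.16625 = 91 events. The odds ratio per SD detectable with 80% power, two-sided 5%, unadjusted, is

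exp[(1.96 + 0.842) / √(550 × 0.16625 × 0.83375)] = exp(2.80/8.73) = 1.38.

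**5. Illustration that the two models test different things.** Data sets of 550 were simulated (367 with PCI, 183 without, 16.6% events, 2,000 per row), and Wald p < 0.05 was counted for each single-predictor logistic model. The odds ratios are assumptions; the protocol gives none. The 0.31 SD shift is the appendix's own 132/430.

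| Assumed truth | Outcome on PCI rejects | Outcome on biomarker rejects |
|---|---|---|
| Biomarker OR 1.5 per SD; PCI unrelated to either | about 5% | 93% |
| Biomarker OR 1.5 per SD, level 0.31 SD higher with PCI | 7% | 94% |
| Biomarker OR 1.3 per SD, level 0.31 SD higher with PCI | 5 to 6% | 63% |
| Biomarker unrelated; PCI OR 1.5 | 34% | 5% |
| Biomarker unrelated; PCI OR 0.67 | 41% | 5% |
| Biomarker unrelated; PCI OR 0.5 | 83% | 4 to 5% |

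**The case against.** The strongest reply is that the protocol does commit to the right kind of model. Section 3 names the predictors (the biomarkers), a comparator score (GRACE) and the response (clinical outcome). Form, transformation and covariates are normally left to the SAP, and the covariates behind the multivariate version in section 4 are unnamed, so a biomarker could enter it. The outcome sentence may simply be an extra comparison of the two groups that interest the sub-study; section 4 never says that it tests prognosis.

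Much of this stands, and it rules out three stronger readings.

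- A reader might infer that the sub-study has no intention of relating biomarkers to outcome, so that a prognostic biomarker would inevitably be missed. The model listed in section 3 shows otherwise.
- A reader might infer that the whole section 7.1 question goes unanswered. Its first half, need for PCI, is the primary aim and is properly matched.
- A reader might take the simulated rejection rates as false-positive rates of the plan. They are the power of a PCI test under assumed PCI odds ratios. The protocol never attaches the biomarker hypothesis to that test, so the table shows only, and by construction, that the models differ.

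What does not stand is that this is merely missing detail. The appendix has its own analysis section, and that section fixes a specific contrast for clinical outcomes. Adding a biomarker as a covariate would leave PCI against no PCI as the stated comparison. An SAP that follows the text inherits that contrast; one that supplies the right model goes beyond it.

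**Conclusion.** The concern holds in limited form. In the Statistical analysis section of Appendix VI, the only model with a clinical outcome as response has PCI status as its contrast and names no biomarker. It does not test the prognostic aim. With PCI given by indication, it does not estimate the effect of PCI on outcome. This rests on reading the aims against the methods and needs no numerical assumption.

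The affected aim is secondary within a sub-study whose results section 4 itself calls likely to be hypothesis generating. The primary sub-study aim and the main trial's analysis are untouched. The point deserves correction because it is cheap to correct, not because it threatens the trial's conclusions. The figures of 91 events and a detectable odds ratio of 1.38 per SD assume that the main-trial planning rates carry over to the 550 sub-study patients.

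**What to change.** Replace the outcome sentence in Appendix VI, section 4, with text to this effect:

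> Clinical outcomes will be analysed by logistic regression on the admission level of each biomarker, alone and then adjusted for GRACE 2.0 score and allocated arm. The 12-month primary composite is the lead outcome; the other binary outcomes named in section 3, including in-hospital, 30-day and 6-month MACE, are exploratory. The combined model of all three biomarkers with GRACE listed in section 3 will also be fitted. Estimates will be given with 95% confidence intervals. Outcomes by PCI status will be described only and will not be interpreted as the effect of PCI.

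Transformation, adjustment for troponin and other model details can stay with the SAP. It would help to say there whether CABG patients count as not requiring PCI.

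The change needs no new data: admission samples, GRACE score, arm and outcomes are already collected. The cost is more secondary models. Each outcome needs 3 biomarkers × 2 models + 1 combined model = 7 fits, so the composite and the three MACE time points need 4 × 7 = 28, and other secondary outcomes would add to that. They should be labelled exploratory, without multiplicity control. The wording is best settled before the stored samples are assayed at the end of the study.
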